### Study aim and objectives

The aim of the study is to increase the postoperative mobilization of the patients by giving them continuous feedback on their step count using activity-tracking wristbands. The primary endpoint of this study is the average step count in the first five POD in the intervention and control groups. Secondary endpoints are the percentage of patients in the two groups who master the predefined mobilization (i.e., step-count) targets, assessment of the activity data obtained from the devices (distance, activity time, inactivity, calorie consumption, compliance), assessment of preoperative mobility with the IPAQ [22], length of hospital and ICU stays (from the first POD until day of discharge), number of patients who receive physiotherapy, 30-day mortality, and 30-day overall morbidity according the Clavien-Dindo classification [23].

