### Statistical considerations and sample size calculation

The sample size estimation was based on our results in a pilot study with 30 participants, 25 of whom were analyzed to collect data about standard mobilization on the first 5 PODs following major visceral surgery. Based on those data, an increase in the daily step count by 250 steps/day with an SD of 290 steps/day was estimated. To achieve 80% power with a two-sided *P* value <0.05 and a dropout rate of 12%, the total sample size calculated with a two-tailed, unpaired *t* test was 120 patients with 30 patients in each group. 

The statistical analysis will be done on an intention-to-treat basis and will be performed with Statistical Package for Social Science software version 18.0 (SPSS, Chicago, IL, USA). The Mann-Whitney *U* test will be used to compare continuous variables, and Fisher’s exact test will be used for categorical variables. Two-sided *P* values will always be computed, and a difference will be considered statistically significant at *P* ≤ 0.05. The primary outcome is the average step count over the first 5 PODs of the patients in the intervention and control goups, separated into the laparoscopic and open surgery arms, respectively. Statistical testing of the outcome parameter will be performed using a regression analysis of repeated measures. In addition, the increase of mobilization within the groups will be analyzed using the repeated measures ANOVA. Logistic regression analyses will be computed to identify factors determining the patient cohort that achieved the mobilization targets (secondary endpoint). The following variables will be considered for the regression analysis: age, sex, body mass index (BMI), operative time, oncological versus nononcological indications, type of surgery (pancreatic, liver, intestinal, gastric), preoperative IPAQ score, and technique of surgery (laparoscopic versus open). Factors that are significant in univariate analysis will be further considered for a multivariate regression analysis.

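### The primary endpoint is one feedback-versus-control comparison in one section and two comparisons by surgical approach in another, each judged at 0.05, with no rule for which result decides the trial

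*Protocol article*

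**What the plan says.** The protocol article calls the two surgical strata (laparoscopic and open) arms; within each, patients are randomized 1:1 to feedback or control.

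- **Study aim and objectives:** "The primary endpoint of this study is the average step count in the first five POD in the intervention and control groups". Surgical approach is not mentioned. The stated aim is one question, whether feedback increases mobilization. The abstract likewise sizes the trial on one difference of 250 steps daily, intervention against control.
- **Statistical considerations and sample size calculation:** the same outcome is given for the intervention and control groups, "separated into the laparoscopic and open surgery arms, respectively". The total is 120, with 30 in each of four groups.
- **Threshold, same section:** "a difference will be considered statistically significant at *P* ≤ 0.05". No division of alpha and no order of testing is given.
- **Test, same section:** directly after the outcome is defined, "Statistical testing of the outcome parameter will be performed using a regression analysis of repeated measures". Earlier in the section a general rule says that the Mann-Whitney *U* "test will be used to compare continuous variables". The unpaired *t* test appears only in the sample size calculation.

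**The concern.** The two definitions lead to different trials. Under the first, one comparison across all patients answers the question. Under the second there are two comparisons in separate sets of patients, each with its own 5% error. Nothing says how to call the trial if feedback is significant after laparoscopic surgery but not after open surgery, or the reverse.

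The choice could then be made after the results are known. If a success in either arm were reported as showing that feedback works, the chance of a false claim would be nearly twice the threshold. If both arms were required, the trial would have less power than the planned 80%.

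**Working it through.** **Inputs.** Difference 250 steps/day, SD 290, two-sided 0.05, 80% power, 12% dropout, unpaired *t* test, 30 per group in four groups (statistics section). Standardized difference: 250/290 = 0.862. Completers per group: 30 × 0.88 = 26.4, taken as 26.

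**1. The plan's own sample size.** By the normal formula, n = 2 × (1.960 + 0.842)² × (290/250)² = 21.1, so 22 per group. The *t* test gives 22.1, so 23. After dropout: 22/0.88 = 25, or 23/0.88 = 26.1, so 27. Over four groups that is 100 or 108, against 120 stated. The figure does not reproduce exactly, but the excess is on the safe side.

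**2. Which definition the size fits.** One comparison needs 2 × 23 = 46 completers, or 2 × 27 = 54 patients with dropout. The planned 120 is roughly two such trials. The sizing therefore follows the split definition, while the abstract and aims section describe one comparison.

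**3. False-positive rate by decision rule.** The arms contain different patients, so their tests are independent. With no feedback effect in either arm:

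| Rule for success | Formula | Rate |
|---|---|---|
| One stratified test | 0.05 | 5% |
| Either arm significant | 1 − 0.95² | 9.75% |
| Both arms significant | 0.05² | 0.25% |

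**4. Power on the plan's difference and SD** (*t* test standing in for the regression's feedback effect).

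- One stratified test, 52 v 52, at 0.05: 99.2%.
- One arm, 26 v 26, at 0.05: 86.2%. At 0.025: 78.5%.
- Both arms required at 0.05: 0.862² = 74.3%.
- Holm across the two arms. An arm is significant if its P ≤ 0.025, or if its P lies between 0.025 and 0.05 and the other arm has P ≤ 0.025. With the effect present in both arms: 0.785 + (0.862 − 0.785) × 0.785 = 84.5% per arm. With the effect in one arm only: 0.785 + (0.862 − 0.785) × 0.025 = 78.7%.
- A flat 0.025 in each arm holds the overall error to 1 − 0.975² = 4.9%. Holm keeps it at or below 5%.

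**5. If the SD is not common.** Suppose, as an assumption, that the laparoscopic SD is twice the stated value (580). With equal weights, the SE of the stratified effect is 0.5 × √[2 × (290² + 580²)/26] = 89.9. Then 250/89.9 = 2.78, and power is about Φ(2.78 − 1.96) = 79%. The laparoscopic arm alone at 0.05 has SE 580 × √(2/26) = 160.9, so power is about Φ(1.55 − 1.96) = 34%.

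**The case against.** **The sections may not conflict.** The aims section names a variable and the randomized groups, and never says pooled. The statistics section may only add detail. Much of the design fits two comparisons: the arms are formed before randomization, the step targets differ by arm (500 v 1900 on POD 1), and each of four groups is sized at 30. This explains where the split comes from. It does not say what decides the trial, and the abstract and aim still pose one question.

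**Separate claims may need no adjustment.** If each arm supports only its own claim, each claim has 5% error. That is defensible, but the article does not say that this is the intention. A multiplicity rule could also sit in an analysis plan not shown, so its absence alone is not the point. The point is that the primary comparison is described in two ways.

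**Stronger readings.** A reader might infer that the trial's error rate simply is about 10%. The documents do not support that: no sentence makes significance in either arm a success, and the 0.05 is a threshold per test. A reader might also infer that three tests compete for the endpoint. That does not hold either. The sentence after the outcome definition assigns it the repeated-measures regression, the *t* test serves only for sizing, and the Mann-Whitney rule reads as a general convention for other continuous variables. The repeated-measures ANOVA concerns change within groups.

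**The 99% power may be optimistic.** This stands. The pilot behind the SD had 20 open and 5 laparoscopic patients, and the much higher laparoscopic targets make a common SD doubtful.

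**Conclusion.** The concern holds as an inconsistency in how the primary comparison is defined, together with a missing decision rule. The abstract and aims section give one comparison. The statistics section gives two, at an unadjusted 0.05 each, for one aim. The false-positive rate for that aim could be 0.25%, 5% or 9.75% depending on the rule adopted, and the article does not fix the rule. The 9.75% is conditional on counting either arm as success.

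The error rates rest on independent strata and no effect in either arm. The power figures rest on 26 completers per group and on the stated difference and SD holding in both arms. Because the choice can change whether the trial is called positive, it should be settled before outcomes are analysed by group.

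**What to change.** Align the aims and statistics sections on one deciding test: the feedback effect over PODs 1–5 from the planned repeated-measures regression, with surgical approach (the randomization stratum) as a term, at two-sided 0.05. Report the estimates per arm and the group-by-approach interaction as secondary.

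If separate claims per arm are wanted, declare two co-primary tests, control alpha by Holm, and word the aim to match.

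Under either option, add a clause that the Mann-Whitney test does not decide the step-count endpoint.

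The cost is a few sentences, with no added patients or data. Under the first option the per-arm results become secondary. Under the second, power per arm falls from 86.2% to 84.5% if the effect is present in both arms, or to 78.7% if it is present in only one.

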The control group will wear an activity tracker wristband with a display covered with adhesive tape so that the step count cannot be read. The study nurse will verify the covered display a few times daily. The intervention group will receive an unblinded wristband. The handling of the activity trackers will be explained to the patients, and a predefined mobilization endpoint (step count) for the first 5 PODs will be targeted. The target step count was set at the 85% quartile on the basis of results a previous pilot study (Table 1). Patients older than 75 years of age were excluded from the analysis in the pilot study. The median age of this group was 60 years (IQR 52.5–70.5 years). A major pancreatic resection was performed in 35% of the patients, a major liver resection in 30%, a colorectal resection in 25%, and a gastric resection in 10%. A surgical fellow or a study nurse will assess and monitor the patient twice daily, between 9:00 a.m. and 11:00 a.m. and between 3:00 p.m. and 5:00 p.m., throughout the patient’s hospital stay to read the step count, to ensure its proper use and functioning, and to communicate the automatic feedback results. The study flowchart is shown in Fig. 1.

**Table 1 Tab1:** Mobilization targets in steps per day

	POD 1	POD 2	POD 3	POD 4	POD 5
Open surgery arm (*n* = 20)	500	620	800	1400	1400
Laparoscopic arm (*n* = 5)	1900	2300	2900	3400	3400

*POD* Postoperative day

Data are presented as 85% quartile based on *n* = 25 patients (results of a pilot study)

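### The analysis of which patient factors go with mobilization is written only as a logistic regression on target reached yes/no, which discards step-count information already collected (minor; secondary and exploratory)

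*Protocol article*

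**What the plan says.** Under Statistical considerations and sample size calculation, the article states: "Logistic regression analyses will be computed to identify factors determining the patient cohort that achieved the mobilization targets (secondary endpoint"). It then lists the candidate variables (age, sex, BMI, operating time, oncological indication, organ group, IPAQ score, open or laparoscopic technique) and a step from univariate to multivariate modelling. Randomized group is not on that list.

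The outcome of this model comes from Study aim and objectives: "Secondary endpoints are the percentage of patients in the two groups who master the predefined mobilization (i.e., step-count) targets". The cut is defined under Randomization and procedures: "The target step count was set at the 85% quartile on the basis of results a previous pilot study". Table 1 gives a separate target for each of the five days and each technique, from 20 open and 5 laparoscopic pilot patients.

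The primary endpoint is the average step count over the first five postoperative days. It is kept continuous and tested by a repeated-measures regression. The sample size rests on that scale: "an increase in the daily step count by 250 steps/day with an SD of 290 steps/day was estimated".

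**The concern.** A yes/no outcome cut in the upper tail treats a patient who just misses the target like one who never walked, and most patients fall into one category. When the question is which characteristics go with more or less walking, the distances on either side of the cut carry most of the information. The article links the listed factors to no model that uses them.

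At stake is the sensitivity of the determinants analysis. Moderate determinants would often fail the univariate screen and be reported as unimportant, although the collected data could have shown them. The test of the feedback intervention is not at stake.

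**Working it through.** **The plan's own figure.** Inputs: "an increase in the daily step count by 250 steps/day with an SD of 290 steps/day was estimated"; "To achieve 80% power with a two-sided" test at 0.05; "a dropout rate of 12"%; "120 patients with 30 patients in each group".
- Normal formula: n = 2 × (1.960 + 0.842)² × (290/250)² = 21.1, so 22 per group. The t test needs 23.
- With dropout: 23/0.88 = 26.1, so 27 per group. The stated 30 is slightly larger, which does no harm here.
- Evaluable: 120 × 0.88 = 105.6, about 106 in total or 53 per arm with techniques pooled.

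**How the cut divides the patients.** Assume normal step counts, one cut on the five-day mean, and 15% of controls above it. The 15% follows from the percentile but is not stated.
- The cut lies at z = 1.036, and the planned shift is 250/290 = 0.862 SD.
- Intervention patients above the cut: 1 − Φ(1.036 − 0.862) = 43.1%.
- Expected masters: 53 × 0.15 + 53 × 0.431 = 30.8 of 106 (29%), so about 71% share the other category.

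**Power for one continuous factor.** Set-up: N = 106, half laparoscopic (as the four groups of 30 imply), SD 290 in both techniques, +250 steps in the intervention arm. Table 1 targets average (500 + 620 + 800 + 1400 + 1400)/5 = 944 for open and (1900 + 2300 + 2900 + 3400 + 3400)/5 = 2780 for laparoscopic surgery. The technique gap is therefore taken as 1836 steps. The factor's correlation with steps within technique and arm is assumed. There were 2,000 simulated trials per row, tested at 0.05 (Wald test for the logistic model).

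| Correlation | Logistic on target reached, with arm | Linear on steps, with technique and arm | Gain (points) | Linear on raw steps, factor alone |
|---|---|---|---|---|
| 0.20 | 30% | 53% | 23 | 10% |
| 0.25 | 45% | 73% | 28 | 10% |
| 0.30 | 60% | 89% | 29 | 16% |
| 0.40 | 86% | 99% | 13 | 23% |

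A likelihood-ratio test lifts the first three logistic figures to 32, 48 and 63%, leaving gains of 21 to 26 points.

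**Hand check of the linear column.** Power ≈ Φ(atanh(r) × √103 − 1.96). For r = 0.25: 0.2554 × 10.149 − 1.96 = 0.632, and Φ(0.632) = 74%. For 0.20 and 0.30 the same formula gives 54% and 88%.

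**Why technique must be in the model.** Without it, the total SD is √(290² + 918² + 125²) = 971, where 918 and 125 are half the technique gap and half the treatment effect. A correlation of 0.25 shrinks to 0.25 × 290/971 = 0.075. This explains the last column: a univariate screen on raw steps would do worse than the planned logistic model.

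**Sensitivity.** If the laparoscopic SD were three times larger (assumed), logistic power for the first three rows is 30, 42 and 57% and adjusted linear power is 44, 63 and 80%. The gain falls to about 14 to 23 points.

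**The case against.** The strongest reply is that reaching the target is a question of its own. The targets are part of the intervention, they were fixed from the pilot before the trial, and the article's discussion is explicitly interested in redefining mobilization targets. That stands: the mastery percentage is a legitimate prespecified secondary endpoint, and a model of who attains it answers a real question. It is a reason to keep that analysis, not a reason to have no continuous one beside it.

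Second, a reader might infer that the cut weakens the trial's test of feedback. At 26 per group (one technique after dropout), Fisher's exact test of mastery at 15% versus 43.1% has 50.2% power, against 86.2% for a t test on steps. The arithmetic is right under the same assumptions, but the inference fails. The primary analysis already compares the groups on the undivided step count within each technique, so the treatment question loses nothing. That 36-point gap must not be attached to the factor analysis.

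Third, mastery against technique-specific targets removes the large open-laparoscopic difference, whereas raw steps do not. This also stands and shapes the fix.

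Fourth, the article is condensed and says only that the variables will be considered for the regression analysis. The nearest model named is the logistic one, and no continuous factor model is mentioned. A fuller analysis plan may contain one, in which case the point is met.

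**Conclusion.** The point holds as a minor one. As written, the determinants analysis rests on a yes/no cut in the upper tail of a variable measured on a continuous scale. For factors correlated 0.2 to 0.3 with steps, logistic power is roughly 30 to 60%, against 53 to 89% for a linear model adjusted for technique and arm.

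This rests on normal step counts, SD 290, one cut on the five-day mean, 15% of controls above it, about 106 evaluable patients, and factor effects that the article does not supply. The gain is smaller for very strong factors, where both methods near their ceiling, and with a larger laparoscopic SD. The direction holds in every setting tried, provided technique is in the continuous model.

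The documents do not support a claim that the primary comparison is underpowered by this choice, or that the mastery endpoint is improper and should be dropped.

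**What to change.** In the statistical section, make the main determinants model a regression of the continuous step count on the listed factors, for example by adding them to the repeated-measures regression already planned. Surgical technique and randomized group should be in every such model, including the one-factor-at-a-time screen.

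An alternative outcome is step count as a percentage of the day- and technique-specific target. This suits data whose spread grows with the level; randomized group should still be included.

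Keep the percentage mastering the targets, with a confidence interval, and the logistic model as the prespecified supportive report of target attainment.

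The cost is a change of wording and one extra model on data already collected, with no additional patients or procedures. The small downside is that factor effects are then expressed in steps or percent of target, with the odds of attainment shown only in the supportive model.

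### Surgical technique is screened as a determinant of reaching targets that were themselves set separately for each technique, so its odds ratio cannot be read as an effect of technique on mobilization

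*Protocol article*

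**What the plan says.** Protocol article, Randomization and procedures: "The target step count was set at the 85% quartile on the basis of results a previous pilot study". Table 1 gives two rows of daily targets for postoperative days (POD) 1 to 5, labelled "Open surgery arm (*n* = 20") and "Laparoscopic arm (*n* = 5"). Its footnote reads "Data are presented as 85% quartile based on *n* = 25 patients (results of a pilot study"). I read the 85% quartile as the 85th percentile, taken within each row's own patients.

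Study aim and objectives makes mastery a secondary endpoint: "percentage of patients in the two groups who master the predefined mobilization (i.e., step-count) targets".

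Statistical considerations and sample size calculation plans logistic regression to find what determines membership of the group that reached the targets. Eight candidates are listed, ending with "preoperative IPAQ score, and technique of surgery (laparoscopic versus open"). Candidates significant in univariate analysis go forward to a multivariate model. The article gives no common target for both techniques and no limit on how the technique coefficient may be read.

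**The concern.** Two stated choices work against each other. The target adjusts for technique, because each surgical arm is judged against its own pilot distribution. The regression then asks whether technique determines success against that target. If the percentiles are right, about 15% of standard-care patients succeed in either arm, however many more steps one arm takes. The effect a reader would look for has been scored out of the outcome.

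What remains in the coefficient includes the error in the two pilot percentiles, and one of them rests on five patients. The trial could report that laparoscopic or open surgery determines reaching the mobilization target when the result mainly shows that one arm's target was set too low or too high. Selection by univariate significance makes it likely that such an artefact is carried into the multivariate model.

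**Working it through.** The protocol gives no figure for this analysis that could be reproduced, so the check starts from Table 1.

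**Inputs from the protocol.** Open targets 500, 620, 800, 1400, 1400 (n = 20). Laparoscopic targets 1900, 2300, 2900, 3400, 3400 (n = 5). Two-sided significance at 0.05. Thirty patients in each of four groups, so 60 per technique. Assumed feedback effect 250 steps/day with SD 290, so 250/290 = 0.862 SD.

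**Assumptions added here.** Normal step counts, one target per stratum, and mastery meaning that this target is exceeded.

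**1. How far apart the targets are.** Laparoscopic divided by open, POD 1 to 5: 1900/500 = 3.80; 2300/620 = 3.71; 2900/800 = 3.63; 3400/1400 = 2.43; 3400/1400 = 2.43.

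**2. Error-free targets.** The 85th percentile lies at z = 1.036.
- Without feedback: 15% v 15%, odds ratio 1.0.
- Half of each stratum shifted by 0.862 SD: 0.5 × 0.15 + 0.5 × [1 − Φ(1.036 − 0.862)] = 29% in both strata, odds ratio 1.0.

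Neither result depends on how far apart the true step counts of the two techniques are.

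**3. What a common target would show.** Apply the open 85th percentile to both techniques, in control patients. If laparoscopic counts are higher by d SD, the odds ratio is {p/(1 − p)}/(0.15/0.85) with p = 1 − Φ(1.036 − d).

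| d (SD) | p | Odds ratio |
|---|---|---|
| 0.5 | 29.6% | 2.4 |
| 1.0 | 48.5% | 5.3 |
| 1.5 | 67.9% | 12.0 |

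Technique-specific scoring removes this difference.

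**4. Pilot error.** In 40,000 simulated pilots, the 85th percentile was estimated from 5 and from 20 patients under two percentile definitions. The true chance of exceeding each estimate was then computed.

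| Definition | Control mastery, n = 5 (95% range) | Control mastery, n = 20 (95% range) | Technique odds ratio (95% range) |
|---|---|---|---|
| Linear interpolation | 3% to 60% | 5% to 36% | 0.13 to 11.2 |
| Weibull (the maximum, for n = 5) | 0.5% to 52% | 4% to 32% | 0.03 to 10.9 |

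The Weibull entry for n = 5 can be checked by hand. The chance of exceeding the maximum of five follows Beta(1, 5), with limits 1 − 0.975^(1/5) = 0.005 and 1 − 0.025^(1/5) = 0.522. This holds for any continuous distribution.

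**5. Consequence for the screening test.** Drawing 60 v 60 patients from these mastery rates and applying a two-sided 0.05 score test (a stand-in for univariate logistic regression) gives significance in about 45% of simulated pilots under either definition. With the same standardized feedback effect in both strata the figure is 47% to 50%.

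**6. Sources other than pilot error.** Keep the targets error-free and let feedback add 250 steps in both strata, but let the laparoscopic SD be 2 or 3 times the open SD (assumed; the protocol gives one SD). The standardized shift falls to 0.431 or 0.287. Mastery is then 21% or 19% v 29%, and the odds ratio is 0.65 or 0.57.

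**The case against.** A reader might infer that the technique odds ratio is nothing but pilot sampling error and holds no effect of technique. The protocol does not support that. The regression covers all patients, half of whom receive feedback, so a different response to feedback by technique would move the odds ratio even with perfect targets. So would a different spread of step counts (step 6). The value of 1 holds for standard-care patients, or when feedback has the same standardized effect in both arms.

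A reader might also infer that the comparison of mastery between feedback and control is compromised because two sets of targets are pooled. It is not. Randomization is 1:1 in blocks and stratified by technique, so both groups carry the same mix of targets. A higher step number is also not a harder target when each is its own stratum's percentile.

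Two further objections stand in part. A technique term in a pooled model is useful, since it absorbs miscalibration between the two target sets and protects correlated factors such as operative time and type of surgery. That argues for keeping the term and not interpreting it. And the simulation simplifies: Table 1 has five targets, which look rounded, with POD 4 and POD 5 identical. The exact range depends on the assumptions, but the circularity does not.

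The point is not one of detail left to a fuller document. The article itself fixes technique-specific targets and names technique as a determinant.

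**Conclusion.** The concern holds as a matter of interpretation. Mastery is standardized by technique, so the planned technique odds ratio cannot be read as an effect of technique on mobilization. Pilot error alone gives it a 95% range of about 0.13 to 11 and makes a 60 v 60 test significant about 45% of the time, assuming normal step counts and one target per stratum. Feedback response and spread by technique may add to it, so the coefficient has no single meaning. The issue is confined to one of eight candidates in an exploratory analysis of a secondary endpoint. The primary endpoint, the sample size and the randomized comparisons are unaffected. The change is worth making because the misleading result is foreseeable and avoiding it costs almost nothing.

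**What to change.** In Statistical considerations and sample size calculation:

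- Remove technique from the list of screened and interpreted determinants of mastery.
- Keep it in the pooled logistic model as a forced stratification term, whatever its P value, and state that its coefficient is not interpreted.
- Report mastery percentages within each surgical arm as well.
- If technique is of interest, estimate its association with the step count itself.

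A forced term in the pooled model is preferable to separate regressions by arm. At the 29% mastery rate of step 2, each arm would have about 0.29 × 60 = 17 achievers, few for the seven remaining candidates.

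The cost is wording only, with no new data and no change to the endpoint. The one loss is an interpretable technique odds ratio for mastery, which the present plan does not provide either.

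### The logistic model for reaching the mobilization targets leaves out randomized group and selects factors by univariate significance on few events; group and surgical approach should be forced in and the screen dropped

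*Protocol article*

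**What the plan says.** All of the following is in the protocol article.

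- **Purpose of the model** (Statistical considerations and sample size calculation): "Logistic regression analyses will be computed to identify factors determining the patient cohort that achieved the mobilization targets (secondary endpoint").
- **Candidates** (same section): "age, sex, body mass index (BMI), operative time, oncological versus nononcological indications, type of surgery (pancreatic, liver, intestinal, gastric), preoperative IPAQ score", and finally "technique of surgery (laparoscopic versus open"). That is eight variables. Randomized group is not among them.
- **Selection rule** (same section): "Factors that are significant in univariate analysis will be further considered for a multivariate regression analysis".
- **Endpoint being modelled** (Study aim and objectives): "the percentage of patients in the two groups who master the predefined mobilization (i.e., step-count) targets". The endpoint is thus framed as a comparison of the randomized groups.
- **Targets** (Randomization and procedures): "The target step count was set at the 85% quartile on the basis of results a previous pilot study". Table 1 sets them separately by technique: 500 to 1400 steps per day for open surgery (20 pilot patients) and 1900 to 3400 for laparoscopic surgery (5 pilot patients).

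The statistical section also assigns Fisher's exact test to categorical variables, which covers the crude comparison of attainment between groups.

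**The concern.** Three features of this model work against its purpose.

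1. It looks for determinants of reaching the target but does not list the one factor the trial manipulates in order to raise step counts. The list is spelled out down to the four levels of type of surgery, so the absence is part of what the article fixes.
2. Entry to the multivariable model depends on univariate significance. With few events, such a screen misses real factors, admits some null ones, and exaggerates the coefficients of those it keeps.
3. Technique is a candidate predictor of an outcome whose threshold already depends on technique.

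At stake is a secondary, exploratory result: the published list of factors, and the chance to report a feedback effect on attainment adjusted for the stratification factor. The primary endpoint is not affected.

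**Working it through.** **The plan's own figures.** The article gives no event count for this model, so there is none to reproduce. Its only sample-size figure is 30 per group (120 in total) for the step-count *t* test. With a difference of 250, SD 290, 80% power and two-sided 0.05, the exact *t* test needs 23 per group, and 23/0.88 = 26.1, so 27 after 12% dropout. The stated 30 exceeds that, and nothing below depends on the gap.

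**Parameters.** Age 1, sex 1, BMI 1, operative time 1, indication 1, type of surgery 3 (four levels), IPAQ 1, technique 1: total 10. Adding randomized group makes 11.

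**Attainment rates (assumed, not stated).**
- Controls: a target at the 85th percentile of standard-care pilot counts implies 15% on a given day.
- Feedback: a normal shift of 250/290 = 0.862 SD gives P(Z > 1.036 − 0.862) = 0.431.

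**Events per candidate parameter**, using 60 per group as randomized, or 53 after dropout (120 × 0.88 = 105.6, about 106 in total):

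| Scenario | Events | Per parameter (10) | With group (11) |
|---|---|---|---|
| N = 120, 15% and 43.1% | 60 × 0.581 = 34.8 | 3.5 | 3.2 |
| N = 106, 15% and 43.1% | 53 × 0.581 = 30.8 | 3.1 | 2.8 |
| N = 120, no effect | 60 × 0.30 = 18.0 | 1.8 | 1.6 |
| N = 106, no effect | 53 × 0.30 = 15.9 | 1.6 | 1.4 |

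With feedback attainment of 30% to 50%, the figure with 10 parameters is 2.4 to 3.9.

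**Definition of attainment.** The article does not say whether the target must be met every day, on any day or on average. Taking five exchangeable days with an assumed correlation of 0.3 to 0.9 and N = 106:
- every day: 4 to 19 events, 0.4 to 1.9 per parameter;
- any day: 44 to 69 events, with the rarer outcome numbering 37 to 52, so 3.7 to 5.2 per parameter.

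**Effect of omitting group on the other coefficients.** For small effects, the attenuation factor is E[p(1−p)] / [p̄(1−p̄)].
- Numerator: (0.15 × 0.85 + 0.431 × 0.569)/2 = 0.186.
- p̄ = (0.15 + 0.431)/2 = 0.2905; denominator: 0.2905 × 0.7095 = 0.206.
- Ratio: 0.186/0.206 = 0.90, a loss of about 10% on the log odds ratio scale.

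**Univariate screen.** With eight independent null factors tested at 0.05, P(at least one selected) = 1 − 0.95^8 = 0.337. If one of the eight is real, the seven nulls give 1 − 0.95^7 = 0.302.

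In a 600-run simulation (N = 106, group omitted, one real factor with log odds ratio 0.50 per SD), the real factor passed the screen in 57% of runs. Its mean estimate when selected was 0.64, and 0.64/0.50 = 1.28. A repeat with eight independent normal covariates (1,500 runs) gave 50% and 0.65. The inflation is therefore similar in both, while the selection rate depends on the set-up.

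**Technique.** The outcome is scored against a different threshold in each technique, and one threshold rests on 5 patients ("Laparoscopic arm (*n* = 5")). If the 85th percentile of five values is taken as the largest, its 90% interval in population percentiles runs from 0.05^(1/5) = 0.549 to 0.95^(1/5) = 0.990. That is only illustrative, since common interpolation rules place it between the fourth and fifth values. It also means that 15% control attainment is least secure in the laparoscopic stratum.

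**The case against.** A reader might infer that the plan ignores its own intervention for this endpoint. It does not. Attainment is defined by randomized group and Fisher's exact test applies to it; the logistic model asks a different question. A reader might also infer that leaving out group biases the other factors. Randomization keeps baseline factors roughly independent of group, so the result is mild attenuation, not confounding. Both replies stand and narrow the point.

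The numbers are open to challenge as well. The figure of about 3 events per parameter rests on normality, one SD and one shift applied to two very different target sets, and an undefined attainment rule. The 34% needs eight independent factors, all null, whereas operative time, type of surgery, technique and indication are plausibly correlated, which would lower it; it also describes the screen, not the final model. These objections hold, and the figures are therefore given as assumption-based ranges. No reading considered exceeds about 5 per parameter, which is thin for selection by significance.

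The tempting claim that the technique coefficient is mostly an artefact of target-setting has not been computed, and the article gives no data to show it. What stands is that it is partly so. A technique term is still needed to absorb the difference in targets.

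Finally, the article's wording is soft (factors are to be considered), and a fuller analysis plan might force terms in. That is possible, but the point rests on the list and rule that the article does state.

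**Conclusion.** The point holds in limited form. For a secondary, exploratory model, the article lists eight variables without randomized group and carries factors forward by univariate significance.

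- **Omission of group:** it drops the expected main determinant, attenuates the other log odds ratios by roughly 10% (if attainment is 15% versus 43%), and forgoes a stratum-adjusted feedback effect.
- **Screen:** it inflates surviving coefficients, by a little under a third in the simulated case, and carries up to about a 34% chance of at least one false selection if all eight factors are null and independent.
- **Information:** about 3.1 to 3.5 events per candidate parameter under the derived rates, and about 0.4 to 5.2 across definitions of attainment. These figures are derived, not stated in the article.
- **Technique:** its coefficient partly reflects where the targets were set and should not be read as a patient factor.

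The primary endpoint, the sample size and the crude group comparison of attainment are unaffected.

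**What to change.** Amend the description of the logistic analysis as follows.

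1. Force randomized group and surgical approach (the stratification factor) into the model.
2. Add a short prespecified covariate set, for example age and IPAQ score, and drop the univariate screen.
3. Report the adjusted group odds ratio alongside Fisher's exact test.
4. Report the other factors as exploratory, with confidence intervals and no significance filter, and do not interpret the technique coefficient.
5. State whether attainment means every day, any day or the average, since the event count depends on it.

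The cost is wording only: all variables are already planned to be collected and no further patients are needed. The downside is that fewer candidate factors can be examined.
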